##### PRIMARY EFFICACY PARAMETER AND ANALYSIS OF ANTIBODY RESPONSE

The study is powered to detect differences between the experimental group and the control group in Pneumococcal vaccine high responders defined as 2-fold increase and IgG levels ≥1 µg/mL to at least 5 of 7 pneumococcal serotypes (by quantitative IgG measurements). The study is not powered to detect differences in the incidence of pneumonia or confirmed pneumococcal disease invasive/non-invasive. This would require a substantial number of participants and a longer follow-up period. The most widely used measurement of immune response to pneumococcal vaccination is quantitative detection of serotype specific anticapsular antibodies. Recent data indicate that the specificity of this method can be improved by incorporation a 22Fabsorption step; thereby removing crossreacting antibodies of low avidity{{13 Feikin,D.R. 2004; }}. Quantitative measurements are done at Statens Seruminstitute, Copenhagen.

##### SECONDARY EFFICACY PARAMETER AND ANALYSIS OF ANTIBODY RESPONSE

Measuring the quantitative amount of serotype specific anticapsular antibodies does not give any information the functionality of the antibodies. This can be measured by a flow-cytometric opsonophagocytic assay and gives indirect information on the antibodies ability to opsonize and facilitate killing of invading pneumococci{{75 Martinez,J.E. 2006; }}. The result of a recent WHO seminar held in January 2007 on standardization of opsonophagocytic assays is expected to be published soon and any possible changes to the method described below will be incorporated.

*Qualitative* analysis are done using a flowcytometric opsonophagocytic assay which measures functional (opsonophagocytic) activity (OPA) of the serotype specific antibodies. In short: Eight twofold dilutions are made in OPA buffer from 10 μl of test serum. A 20-μl aliquot of either multiplex bacteria or multiplex bead suspension containing 1x105 of each of the target pneumococcal serotype or pneumococcal polysaccharide-conjugated beads is added to each

well, and the plate is incubated for one hour at 37°C with horizontal shaking (200 rpm). Following this, 20 μl of sterile serum from 3- to 4-week-old baby rabbit serum (Pel-Freez, Brown Deer, Wis.) is added to each well except for HL60 cell control wells, which receives 20 μl of OPA buffer. After incubation at 37°C for 20 min with shaking (200 rpm on an orbital shaker), 30 μl of washed HL60 polymorphonuclear leukocytes (PMNs) (2.5 μ 104/ml) are added to each well, resulting in an effector-to-target ratio of 1:4 (for each target type). The final well volume is 80 μl, with the first well of a dilution series containing a 1:8 final dilution. The plate is then incubated for 60 min with shaking at 37°C. An additional 80 μl of OPA buffer is added to every well to provide sufficient volume for flow cytometric analysis and the well contents transferred to microtiter tubes (Bio-Rad, Hercules, Calif.). Up to 12 serum samples can be assayed per plate, including a quality control sample. Flow analysis are done by Flow Applications, Inc, Ill, USA{{75 Martinez,J.E. 2006; }}.

##### PNEUMOCOCCAL CARRIAGE

Pneumococcal vaccination can affect pharyngeal carriage of pneumococci. Pneumococcal pharyngeal colonization may also affect the immune response to pneumococcal vaccination{{86 Frazao,N. 2005; }}. Therefore it is important to establish carrier status before and after pneumococcal vaccination. Oropharyngeal colonization will be tested in the posterior pharynx using a BBL culture swap (Becton Dickson Microbiology Systems, Cockeysville, MD, USA) thru the oral cavity. Samples will be labeled with the individuals study ID number, frozen at -20°C within few hours and later shipped to Statens Serum Institut, where isolation, culturing and serotyping will take place. This will take place at day 0 and again during follow-up at day 270.

##### SAFETY/TOLERABILITY ASSESSMENT PARAMETERS:

The investigator is responsible for the detection and documentation of events meeting the criteria and definition an adverse event (AE) or serious adverse event (SAE) as provided in the protocol. During the study, when there is a safety evaluation, the investigator or site staff will be responsible for detecting AEs and SAEs, as detailed in this section of the protocol.

Each subject will be instructed to contact the investigator immediately should the subject manifest any signs or symptoms they perceive as serious.

##### ADVERSE EVENTS (AEs):

An AE is any untoward medical occurrence in a clinical investigation subject, temporally associated with the use of a medicinal product, whether or not considered related to the medicinal product.

An AE can therefore be any unfavorable and unintended sign (including an abnormal laboratory finding), symptom or disease (new or exacerbated) temporally associated with the use of a medicinal product.

In this study an AE will be graded according to the Common Toxicity Criteria, version 2.0. The criteria are located in the Appendix 2.

##### SERIOUS ADVERSE EVENT (SAE) DEFINITION:

An adverse event occurring during a clinical trial is any undesirable experience associated with the use of a medical product in a participant. The event is serious and will be reported to the regulatory authority when the participant outcome is:

1. Death
2. Life-Threatening
3. Hospitalization (initial or prolonged)
4. Disability
5. Requiring Intervention to Prevent Permanent Impairment or Damage
6. Congenital disorder/anomaly (for pregnant women)

In this study we will follow a cohort of 94 HIV-infected individuals for 10 months each giving a total observation time of approximately 78 person years. As noted in the background section of this protocol HIV-infected individuals have a much higher morbidity and mortality than an aged-matched background population. Thus, we can expect to have anywhere between 10 and 20 SAEs during the time of the study. All of these SAEs will be investigated to determine if the event fulfills criteria for being a SUSAR.

##### SUSPECTED UNEXPECTED SERIOUS ADVERSE EVENT REACTION (SUSAR) DEFINITION:

A Suspected Unexpected Serious Adverse Reaction (SUSAR) occurring during the study and is vil be reported to the Danish Medicines Agency on a **Council for International Organizations of Medical Sciences** (CIOMS) form (Appendix 3):

- The event must be a SAE.
- There must be a certain degree of probability that the event is an adverse reaction on the administered drug.

The adverse reaction must be unexpected, that is to say, not foreseen in the Investigator’s Brochure (for an unauthorised medicinal product) or in the summary of product characteristics (for Prevenar and Pneumo Novum).

##### SUBMITTING SUSPECTED UNEXPECTED SERIOUS ADVERSE EVENT REACTION (SUSAR) REPORTS

The investigator will report a SAE/SUSAR to the sponsor within **24 hours of his/her becoming aware of the event.** SUSARs will be reported to the Danish Medicines once the sponsor determines that the event meets protocol definitions of a SUSAR. The sponsor will fax the SUSAR report/CIOMS form to the Danish Medicines Agency **within 7/15 DAYS of his becoming aware of the event.** The investigator will provide an assessment of causality at the time of the initial report. In the event of a death determined by the investigator to be related to vaccination/test drug a fax must be sent to the study monitor.

CLINICAL LABORATORY PARAMETERS AND OTHER ABNORMAL ASSESSMENTS QUALIFYING AS ADVERSE AND SERIOUS ADVERSE EVENTS

Abnormal laboratory findings or other abnormal assessments (i.e. by physical examination) that are judged by the investigator to be clinically significant will be recorded as AEs or SAEs if they meet the criteria outlined above. Clinically significant abnormal laboratory findings or other abnormal assessments that are detected during the study or are present at baseline and significantly worsen following the start of the study will be reported as AEs or SAEs.

The investigator will exercise his or her medical and scientific judgement in deciding whether an abnormal laboratory finding or other abnormal assessment is clinically significant.

##### FOLLOW-UP OF ADVERSE EVENTS AND SERIOUS ADVERSE EVENTS AND ASSESSMENT OF OUTCOME

After the initial AE/SAE report, the investigator is required to proactively follow each subject and provide further information to the study group on the participant’s condition.

All AE/SAEs documented at a previous visit/contact and designated as not recovered/not resolved or recovering/resolving will be reviewed at subsequent contacts/visits.

Investigators will follow-up subjects:

- With SAEs or subjects withdrawn from the study as a result of an AE, until the event has resolved, subsided, stabilized, disappeared, the event is otherwise explained, or the subject is lost to follow-up;
- Or, in the case of other non-serious AEs, until they complete the study or are lost to follow-up

Clinically significant laboratory abnormalities will be followed up until they have returned to normal, or a satisfactory explanation has been provided. Additional information (including, but not limited to, laboratory results) relative to the subsequent course of such an abnormality noted for any subject must be made available to the Study Monitor.

Outcome of any non-serious adverse event occurring within 30 days post-vaccination, any specific AEs (new onset of chronic illness, rash, events prompting emergency room visit and/or physician office visit for non-routine care and any event related to vaccine efficacy (i.e. pneumococcal disease) or any SAE reported during the entire study will be assessed as:

- Recovered/resolved
- Not recovered/not resolved
- Recovering/resolving
- Recovered/resolved with sequelae
- Fatal (SAEs only)

##### TREATMENT OF ADVERSE EVENTS

Treatment of any adverse event is at the sole discretion of the investigator and according to good medical practice. Any medication administered for the treatment of an AE should be recorded in the subjects CRF.

##### SAFETY UPDATES

A periodic safety update report (PSUR) is a report describing the safety of a medicinal product. The primary investigator will submit a PSUR once annually to the Danish Medicines Agency and the regional ethical comiteé until the trial is completed. Among other things, such a report will include a list of the adverse reactions known to the sponsor, an estimate of the number of humans treated with the medicinal product (CPG 7909), an overall assessment of the medicinal product’s safety profile suggestions for new initiatives as regards safety, if relevant

***After the trial has ended a complete safety and study report will be submitted to the Danish Medicines Agency and Coley Pharmaceutical Group, Inc.***

DMA

**Reporting Serious Adverse Events
during the *ITAP study***

Sponsor

Investigator

All investigators

Coley P.G.

DMA.

Reg. Ethical Committee

SAEs according to definitions

in the study protocol

List of all SUSARs every 6 months

According to the pharmaco-

vigilante agreement provided By Coley Pharmaceutical Grp

List of all SAEs once annually + report on the safety of study participants

All SUSARs reported within 7/15 days using a CIOMS form

List of all SAEs once annually + report on the safety of study participants

*SAE: Serious Adverse Event*

*SAR: Serious Adverse Reaction*

*SUSAR: Suspected Unexpected Adverse Reaction*

*DMA: Danish Medicines Agency*

##### SOLICITED ADVERSE EVENTS

A four day follow-up (day 1 to 4) of solicited local (injection site) and general adverse events will be performed after study vaccine administration. Data concerning the AEs will be solicited using diary cards provided by the sponsor-investigator and AEs will be listed as detailed on page 25.

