The safety profile of several TLR9 agonists in humans has been observed in the clinical trials described above over a more than 1,000-fold dose range from 0.0025–0.81 mg per kg. A maximal tolerated dose in humans has not been reported to date. The primary adverse events are dose-dependent local injection reactions (such as erythema, pain, swelling, induration, pruritus or warmth at the site of injection) or systemic flu-like reactions (such as headache, rigors, myalgia, pyrexia, nausea and vomiting), and are consistent with the known TLR9 agonist mechanism of action. Depending on the dose, systemic symptoms typically develop within 12–24 hours of dosing and persist for 1–2 days. At the low doses used in vaccine trials there seems to be a slight increase in the frequency of injection-site reactions, which are generally mild, above the frequency observed with the vaccine alone. The clinical experience to date indicates that CpG ODN treatment of normal humans, cancer patients or individuals infected with HIV or HCV does not readily induce autoimmune disease.

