**UNSOLICITED ADVERSE EVENTS**

During the entire study period (from day 0 to month 10) follow-up will be conducted for the occurrence of specific AEs which consist of the following:

- New onset of chronic illness(es) (e.g., autoimmune disorders, asthma, type I diabetes)
- Rash (i.e. hives)
- Any conditions prompting any ER/non-routine physician office visits (i.e. office visits not related to well-child care, vaccination, injury or common acute illnesses such as upper respiratory tract infections, otitis media, pharyngitis, gastroenteritis)

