**SECONDARY ENDPOINTS:**

**REACTOGENICITY AND SAFETY IN ALL SUBJECTS**

**ANALYSIS POPULATIONS:**

**Safety population:** all patients who received at least one vaccination.

- Occurrence of solicited and general symptoms during the 4-day (day 0 to Day 3) period after each vaccination dose
- Occurrence of unsolicited symptoms up to 1 month after each vaccination
- Changes in CD4-count and viral load during the study

Safety will be assessed by physical examination, adverse events (according to common toxicity criteria version 2.0), laboratory tests, and HIV control parameters (HIV RNA and CD4-count).

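### The written adverse-event collection does not match two safety endpoints: the four-day solicited windows disagree, and the one-month unsolicited endpoint has no contact near one month after doses 1 and 2

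*Protocol*

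**What the plan says.** **Solicited events.** The Solicited Adverse Events section describes "A four day follow-up (day 1 to 4) of solicited local (injection site) and general adverse events" and names the tool: "Data concerning the AEs will be solicited using diary cards provided by the sponsor-investigator". The endpoint under Reactogenicity and Safety in All Subjects is "Occurrence of solicited and general symptoms during the 4-day (day 0 to Day 3) period after each vaccination dose".

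**Unsolicited events.** The same endpoint list includes "Occurrence of unsolicited symptoms up to 1 month after each vaccination". The section on follow-up and outcome of adverse events is equally broad, since it covers "Outcome of any non-serious adverse event occurring within 30 days post-vaccination". The Unsolicited Adverse Events section is narrower: "During the entire study period (from day 0 to month 10) follow-up will be conducted for the occurrence of specific AEs". Its list is new chronic illness, rash, and conditions leading to emergency or non-routine physician visits, and visits for common acute illnesses are excluded.

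**Contacts.** Doses are given at days 0, 90 and 270. The Schedule of Assessments records adverse events on each vaccination day and at follow-up on day 90 ± 14, day 270 ± 30 and day 300 ± 30. The day 90 follow-up precedes the second vaccination. Between visits, participants are told to call only about symptoms they perceive as serious.

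**The concern.** Two safety endpoints are defined over windows that the collection text does not serve.

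- If the diary starts the day after vaccination, it has no entry for a day that the solicited endpoint counts. The Background says of TLR9 agonists that "systemic symptoms typically develop within 12" to 24 hours of dosing, so some onsets can fall on the vaccination evening, after the participant has gone home.
- The one-month unsolicited endpoint covers all unsolicited symptoms, but the section that describes their follow-up is limited to specific kinds. After doses 1 and 2 nobody is scheduled to ask until months later.

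This is a phase I trial with safety and tolerance of CPG 7909 as a stated objective, and adverse events are to be reported as proportions with 95% confidence intervals. An event that is never recorded lowers such a proportion directly, and no later analysis plan can recover it.

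**Working it through.** No sample-size figure is involved. The check compares windows and computes intervals from the schedule.

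**1. Solicited window.** Count the vaccination day as day 0, as the schedule and dosing text do for the first dose and the endpoint does for each dose.

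- Diary: days {1, 2, 3, 4}
- Endpoint: days {0, 1, 2, 3}
- In both: {1, 2, 3}; endpoint only: {0}; diary only: {4}

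Both windows last four days. They coincide if the diary section calls the vaccination day day 1. If it does not, one of the four endpoint days has no diary entry.

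What a literal reading loses follows from the Background: systemic symptoms arise at 12–24 hours and persist for 1–2 days. Most would therefore still be present on day 1 or 2, which both windows include. The loss is the onset time, which the case report form requires, and reactions that begin and end on the vaccination day. The post-vaccination stay of at least half an hour does not reach that evening.

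**2. Scope of unsolicited events.**

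| Section | Events | Period |
|---|---|---|
| Safety endpoints | all unsolicited symptoms | 1 month after each dose |
| Follow-up and outcome of AEs | any non-serious AE | 30 days after vaccination |
| Unsolicited Adverse Events | specific AEs only | day 0 to month 10 |

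The first two agree. The third describes a whole-study tier and is silent on the 30-day tier.

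**3. Time from the end of the one-month window to the next scheduled contact.** One month is taken as 30 days, and visit tolerances are treated as independent.

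Gap = day of next visit − (day of dose + 30)

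- Dose 1 (day 0), next visit day 76–104: 76 − 30 = 46 to 104 − 30 = 74 days; nominal 90 − 30 = 60.
- Dose 2 (day 76–104), next visit day 240–300: 240 − (104 + 30) = 106 to 300 − (76 + 30) = 194 days; nominal 270 − (90 + 30) = 150.
- Dose 3 (nominal day 270), visit nominal day 300: 300 − (270 + 30) = 0. With dose 3 on day 240–300 and the visit on day 270–330, the visit can fall before the window closes or up to 330 − (240 + 30) = 60 days after it.

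**4. Share of doses affected.** Planned doses are 94 × 3 = 282. Doses with no scheduled contact near one month are 94 × 2 = 188, two of the three per participant.

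**The case against.** The case on the other side is substantial.

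- **The solicited mismatch may be labelling.** Equal lengths suggest one window counted from 1 in one place and from 0 in another. The participant diary (Appendix 4) is not shown and could settle it. This stands: the text proves an inconsistency, not that the form lacks the vaccination day. That day is not unobserved either, since adverse events are recorded and an examination is made before discharge.
- **The expected CPG 7909 reactions would mostly be caught.** A reader might infer that they fall largely on the vaccination day and go unrecorded. The Background does not support that, because symptoms lasting 1–2 days would usually still appear on day 1.
- **All events within 30 days are already foreseen.** The follow-up and outcome section does foresee them, and subject-reported events are recorded at every visit. So collection after doses 1 and 2 is retrospective, not absent. That section does not say how or when the events are to be elicited, however, and the schedule supplies no contact near one month.
- **Dose 3 is not a clean comparator.** Its gap of zero is only nominal, and no stated endpoint compares doses with one another. Both points stand.
- **Both arms are treated alike.** A reader might infer that CPG 7909 will look safer than it is relative to control. Under double blinding the arms share the same diary, visits and recall interval, so the documents do not support a differential bias.

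**Conclusion.** The point holds in a limited form. The protocol contradicts itself on the solicited window, and its unsolicited section and visit schedule do not serve an endpoint that it states for every dose.

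The solicited part is at least a text conflict. On a literal reading it costs one of four endpoint days, chiefly onset times and brief same-day reactions.

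The unsolicited part carries more weight: for 188 of 282 planned doses, non-serious events in the month after vaccination rest on recall at about three and six months. That is likely to understate absolute proportions and may attenuate a between-arm difference. The documents give no basis for estimating by how much.

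This assumes that one month means 30 days, that visit tolerances vary independently, and that the unseen diary does not already extend to 30 days. Only secondary safety endpoints are affected; the primary endpoint and sample size are not. The change should be made, because unrecorded events cannot be restored at analysis.

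**What to change.** 1. Reconcile the Solicited Adverse Events section and the solicited endpoint to one window that includes the vaccination day. State which number that day carries, and match the diary to it.
2. Align the Unsolicited Adverse Events section with the endpoint list and the follow-up and outcome section: all adverse events to 30 days after each dose, and the listed specific events throughout the study.
3. Add a 30-day unsolicited-event page to the existing diary card, returned after each dose, so that the endpoint is recorded as events happen.

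The cost is a diary reprint, the text alignment and slightly more participant effort. No visits are added.

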**UNSOLICITED ADVERSE EVENTS**

During the entire study period (from day 0 to month 10) follow-up will be conducted for the occurrence of specific AEs which consist of the following:

- New onset of chronic illness(es) (e.g., autoimmune disorders, asthma, type I diabetes)
- Rash (i.e. hives)
- Any conditions prompting any ER/non-routine physician office visits (i.e. office visits not related to well-child care, vaccination, injury or common acute illnesses such as upper respiratory tract infections, otitis media, pharyngitis, gastroenteritis)

##### EVALUATING ADVERSE EVENTS AND SERIOUS ADVERSE EVENTS

##### ASSESSMENT OF INTENSITY

Intensity of AEs will be assessed as outlined in the common toxicity criteria (CTC) version 2.0 (APPENDIX 2).

The investigator will make assessment of the maximum intensity that occurred over the duration of the event in cases where the event was not registered in the participant’s diary (i.e. unsolicited AEs, SAEs, APPENDIX 4). The assessment will be based on the investigator’s clinical judgement.

**ASSESSMENT OF CAUSALITY**

The investigator is obligated to assess the relationship between the investigational product and the occurrence of each AE/SAE. The investigator will use clinical judgement to determine the relationship- Alternative causes, such as natural history of the underlying diseases, concomitant therapy, other risk factors and the temporal relationship of the event to the investigational product will be considered and investigated. The investigator will also consult the Investigator Brochure and vaccine product information in the determination of his/hers assessment.

All solicited local (injection site) reactions will be considered causally related to vaccination. Causality of all other AEs should be assessed by the investigator.

